### Power calculation

The effectiveness of the proposed investment based intervention has been preliminarily examined in the pilot study conducted by Husted and Ogden [16]. The study showed that with only 98 participants (48 in intervention and 50 in the control groups) there was a significant effect of the intervention on weight loss by 3 months follow up with a mean difference of 7 kg between the groups. This resulted in a small / medium effect size (d = 0.3). The present study aims to assess outcomes up to 12 months thus raising the risk of attrition over time. In addition, the study will have a baseline measure of weight pre surgery rather than after surgery. Therefore, assuming an attrition rate of 40% by 12 months with an alpha of 0.05 and a beta of 0.8 we propose to invite 200 participants (100 in each condition) to ensure that data from at least 120 participants is collected at the 12 months follow up (60 in each group). This should provide statistical power to detect a small to medium difference in weight (controlling for baseline weight) by 12 months follow up.

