### Primary outcome measures

BMI and weight: Patients’ weight will be obtained in the clinic to provide the primary baseline and endpoint measure of the trial. This will be collected preoperatively 2 weeks before surgery, immediately after surgery and postoperatively at 3, 6 and 12 months follow up. In addition baseline measures of age, sex, height, type of surgery, educational level, and ethnicity will also be taken.

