### Data analysis

The data will be analysed to explore the impact of the investment based weight loss intervention on patient’s weight and BMI controlling for baseline measures using ANCOVA. Furthermore the impact of the investment intervention will be explored with regard to patients’ beliefs about foods, behavioural intentions and diet and exercise behaviours using repeated measures ANOVA. Finally the data will be analysed to assess the role of changes in beliefs about food, behavioural intentions and behaviour in predicting weight loss by follow up using mediation analysis. Any baseline differences will be included as covariates in the analysis where necessary.

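### The stated weight analysis, read as a 12-month ANCOVA, makes no use of the 3- and 6-month weights of patients lost before 12 months; a model of all visits would recover some precision and guard against arm-specific dropout

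*Protocol article*

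**What the plan says.** Four statements in the protocol article bear on this point.

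- **Data analysis, weight.** The method is "weight and BMI controlling for baseline measures using ANCOVA". No visit is named.
- **Data analysis, secondary outcomes.** A repeated-measures method appears only here: "behavioural intentions and diet and exercise behaviours using repeated measures ANOVA".
- **Power calculation.** The aim is to "detect a small to medium difference in weight (controlling for baseline weight) by 12 months follow up", "assuming an attrition rate of 40% by 12 months". So 200 patients are invited in order to have 120 (60 per arm) at 12 months.
- **Primary outcome measures.** Weight is taken in clinic before surgery, then "immediately after surgery and postoperatively at 3, 6 and 12 months follow up".

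Taken together, these point to an ANCOVA of 12-month weight on baseline weight in patients who have a 12-month weight. The article describes no use of interim weights for the other patients. Its only stated response to attrition is to invite more patients.

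**The concern.** The plan expects 80 of 200 patients to have no 12-month weight. Some of them will have been weighed at 3 months, or at 3 and 6 months. Those weights should carry information about where the patient would have been at 12 months, and a single-visit ANCOVA does not use it.

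Two things are at stake. The first is precision. The second is protection against selective loss: recruiting extra patients replaces numbers, but it does not correct for who leaves. The trial is open, and only the intervention arm is asked at 3 and 6 months to reflect on pain, disruption and cost. Patients who are doing poorly could therefore leave at different rates in the two arms. The 6-month weight, which could adjust for this, is already being collected.

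**Working it through.** **1. The plan's own figure.** 120 / (1 − 0.40) = 200, so the attrition allowance reproduces. The loss is budgeted in numbers.

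**2. Precision.** Inputs from the article: 100 per arm at the start and 60 per arm at 12 months. Assumed, because the article does not give them:

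- n3 and n6 per arm still seen at 3 and 6 months;
- monotone dropout;
- correlation r between adjacent visits given baseline, and r² between 3 and 12 months.

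With unit residual variance and known covariance, a model of all visits gives the 12-month arm mean the variance

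V = (1 − r²)/60 + r² × [(1 − r²)/n6 + r²/n3],

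against 1/60 for completers only.

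Example with n3 = 85, n6 = 72, r = 0.8:

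- bracket = 0.36/72 + 0.64/85 = 0.01253
- V = 0.36/60 + 0.64 × 0.01253 = 0.01402
- effective n = 1/0.01402 = 71.3 per arm
- variance ratio = 60 × 0.01402 = 0.841, a 16% reduction (about 8% in the standard error)

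Reduction in variance across the assumed range:

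| Seen per arm at 3 / 6 / 12 months | r = 0.5 | r = 0.6 | r = 0.8 | r = 0.9 |
|---|---|---|---|---|
| 70 / 65 / 60 (mostly early loss) | 2% | 4% | 8% | 11% |
| 85 / 72 / 60 | 5% | 8% | 16% | 22% |
| 95 / 85 / 60 (mostly late loss) | 8% | 12% | 22% | 29% |

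The corners correspond to 61 and 84 effective patients per arm, or standard errors smaller by about 1% and 16%.

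**3. Bias.** Simulation with no true effect, 100 per arm, 12-month residual SD 11 kg, 6-to-12-month correlation 0.8 and 40% lost by 12 months. Dropout after 6 months is logistic in the 6-month weight, with a log-odds slope per SD in each arm. All inputs except the 100 per arm and the 40% are assumptions.

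| Slope, control / intervention | Timing of loss | Completer difference | Type I error |
|---|---|---|---|
| 0.5 / 0.5 or 0.8 / 0.8 | all after 6 months | at most 0.1 kg | about 5% |
| 0.4 / 0.6 | all after 6 months | 0.6 kg | about 6% |
| 0 / 0.5 | half early, unrelated to weight | about 1.0–1.1 kg | 8–9% |
| 0 / 0.8 | half early, unrelated to weight | 1.6 kg | 12–13% |
| 0 / 0.5 | all after 6 months | 1.7 kg | 13–15% |
| 0 / 0.8 | all after 6 months | 2.5 kg | 24–25% |

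In these one-arm rows the error favours the intervention, because its heavier patients leave. If the dependence sat in the control arm instead, the error would reverse and could hide a benefit. Conditioning on the 6-month weight brought the bias to about 0. That follows from the set-up, in which late dropout depends only on that observed weight.

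**The case against.** The best defence is that the article does not state a completer analysis. It names ANCOVA and baseline adjustment, but no visit, analysis population or missing-data rule. ANCOVA with multiple imputation from the 3- and 6-month weights would fit the same sentence, and an analysis plan that is not shown may specify it. This stands in part: single-visit completer use is an inference. It is a well-supported one, because the power calculation is tied to patients with 12-month data and repeated measures are named only for secondary outcomes. Reading the sentence as a classical repeated-measures ANCOVA would not help, since that also drops patients without a 12-month weight.

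The precision gain can be small. If most loss is early, the standard error falls by only about 1% to 5%. This stands.

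A reader might also draw three stronger conclusions that the documents do not support:

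- **That only the intervention arm is contacted at 3 and 6 months.** The Design, Control group and Primary outcome measures sections give both arms the same visits, weights and questionnaires. Only the added investment questions differ, so the case for arm-specific dropout is plausible but not strong.
- **That the ANCOVA is valid only if dropout is unrelated to progress.** Equal dependence in both arms left the arm difference essentially unbiased.
- **That 1.7 to 2.5 kg is the expected bias.** Those rows put the dependence in one arm only and all loss after 6 months, which is an extreme scenario.

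**Conclusion.** The point holds as an avoidable weakness in the stated method. It is not an error that invalidates the trial, and attrition was not overlooked. On the natural reading, information already collected goes unused. Its value is roughly a 2% to 29% reduction in the variance of the 12-month contrast, under assumed correlations of 0.5 to 0.9 and assumed dropout timing.

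Bias is possible, not shown. It requires the link between progress and dropout to differ by arm. It is negligible when the link is equal, about 0.6 kg for slopes of 0.4 against 0.6, and reaches 1.7 to 2.5 kg only in the extreme scenario. For scale, the pilot difference cited in the power calculation is a "mean difference of 7 kg between the groups".

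Precision matters here because the margin is thin. With d = 0.3 and two-sided alpha 0.05, 60 per arm gives 37.6% power without baseline adjustment. It reaches 80% only if the baseline correlation, which is not stated, is about 0.81. The sample size is a separate matter, but it leaves little room to give information away.

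**What to change.** In Data analysis, make the primary estimate the 12-month arm difference from a likelihood-based linear mixed model of the 3-, 6- and 12-month weights. Include arm by visit, baseline weight by visit and an unstructured covariance. Fit it in all randomised patients with any follow-up weight, analysed as allocated. Keep the 12-month completer ANCOVA as a sensitivity analysis. If ANCOVA is preferred as the primary method, multiple imputation of missing 12-month weights from the 3- and 6-month weights is an acceptable equivalent. In either case, name 12 months as the visit.

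The cost is a few lines of text and standard software, with no extra patients or measurements. Two limits remain. The model assumes that missingness is explained by baseline and earlier weights, and patients lost before 3 months contribute no follow-up weight.

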## Background

Obesity is caused by people consuming more energy than they expend and is associated with reduced life expectancy and many serious conditions including heart disease, stroke, diabetes, cancer, gallstones, fatty liver disease and sleep apnoea [1,2]. Currently almost two-thirds of UK adults are either overweight or obese with overall costs to society forecast to reach £50 billion per year by 2050 on current trends [2].

Although the most common form of obesity management emphasizes changes in diet and exercise, research indicates that weight loss surgery (WLS) is most effective and this approach is currently recommended for those whose BMI is greater than 40 kg/m2 (or 35 kg/m2 with comorbidities) [3]. A systematic review of WLS [4] concluded that the mean percentage excess weight loss (EWL) for the Roux-en-Y gastric bypass was 67% and for the gastric band was 42% at one year. WLS has also been shown to result in improvements in a number of other patient outcomes including quality of life, mood, subjective health status and perceptions of eating control [5,6].

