Although WLS is currently one of the most frequently performed procedures in the US and Europe [7], questions have been raised about the long-term durability of weight loss as research indicates that a substantial proportion of individuals begin to regain lost weight over time [5,8-10]. In response to growing evidence that WLS does not work for everyone research has attempted to understand this variability. In particular, research has explored the mechanisms involved in successful and failed bariatric surgery to highlight how effectiveness could be improved [11,12]. The results indicate that less successful surgery is associated with feeling unprepared for the changes required after surgery, reporting being unsupported in the time following surgery and a sense that although surgery fixes their body, psychological issues relating to dietary control, self-esteem, coping and emotional eating remain neglected. These studies also explored successful weight loss following surgery and reported a role for a reduction in hunger, a decrease in the preoccupation with food and sense of improved control. Such research also highlights a central role for investment and this is supported by other studies using medical and behavioural interventions. For example, bariatric patients reported that success was associated with a feeling that they had made an investment in their operation in terms of factors such as time of work, financial cost, disruption to family and social life, the pain of the surgery and the process of recovery. As one participant said after surgery ‘the amount of pain, the operations performed. Don’t want to do any damage, don’t particularly want the stomach to enlarge anymore which it can do’. Similarly, research indicates that obesity medication may work through the greater investment needed for adherence due to unpleasant side effects [13]. Further, success from behavioural interventions is associated with perceptions of greater investment in attempts to lose weight such as joining self-help groups or attending organised slimming clubs. From this perspective greater investment into weight loss attempts increases the chances of success by motivating the individual to make the most of the efforts they have made so far and encourages them to maximise the consequences of these efforts.

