Perceived investment therefore motivates change across all areas of obesity management. This perspective finds reflection in the body of work on the effect of financial incentives on behaviour change with greater costs either facilitating positive behaviours or deterring unhealthy behaviours [14]. It is also parallel to research on the placebo effect which illustrates that placebos which involved greater investment (i.e. bigger pills, expensive treatments, painful interventions, lengthy consultations, greater distances travelled) are more effective that those which are easier to take part in [15]. In line with this approach, a recent pilot study explored the impact of manipulating perceived investment in patients just after they had had bariatric surgery [16]. Patients (n = 98) were recruited from an online support group for bariatric patients and were randomly allocated to either the control or intervention group. Those in the intervention group then completed a simple series of carefully framed questions designed to encourage them to consider the investment they had already made in having their operation. For example, they were asked to rate the procedure in terms of their pain experienced, the time spent organising the operation, the disruption to their family and social life, the time needed to recover and the impact of the recovery process on their family and work. This approach was inspired by recent research exploring the ‘mere measurement’ effect which illustrates that simply completing framed questions can change the ways in which people think and behave [17,18]. The results from this pilot study indicated that the investment intervention resulted in an immediate change in participants’ beliefs about food and their intentions to change their diet and exercise behaviour. By three months follow up the investment group reported losing 7 kg more than the control group (a significant difference). This pilot study was small scale and involved patients post-surgery only. In addition, follow up data was only collected in the short term and attrition was high by this time point (probably due to the online nature of the study). The present study aims to develop this investment based intervention using a larger sample, with a longer follow up and involving assessments at both pre and post-surgery in order to generate a proper baseline. Bariatric surgery is therefore the treatment of choice for obese patients. Not all patients, however, lose the desired amount of weight. Research highlights a role for investment which lends itself to a low cost, easy to administer intervention that may promote successful weight loss in the longer term. Therefore the aim of this study is to evaluate the impact of an investment based intervention compared to usual care on patient weight loss, beliefs and behaviours after bariatric surgery.

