
## Methods/Design

### Design

The study will involve an open randomised parallel group control trial with patients allocated either to the control or investment intervention group. All participants will complete measures of their beliefs about food, diet and exercise behaviour, intentions to change their behaviour and weight at baseline (2 weeks pre surgery) and at 3, 6 and 12 months follow up. Those in the investment group will complete carefully framed questions designed to raise the salience of the investment they have made in their procedure at baseline the 3 and 6 months after surgery. The content of this intervention will be tailored to the recent experiences of the patient (i.e. pre or post-surgery). This study has received favourable ethical opinions from the Bloomsbury Research Ethics Committee, National Research Ethics Service UK and the University of Surrey Ethics Committee. The structure and reporting of this trial will be guided by the CONSORT statement for clinical trials [19].

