### Investment intervention group

Those allocated to the investment based intervention will complete the investment based intervention at baseline (2 weeks pre surgery) then 3 and 6 months post-operatively. This intervention is based on the pilot study [16] and involves participants rating questions relating to the investment they have made in having bariatric surgery as a means to raise the salience of their investment. In particular, the questions will encourage patients to consider the ways in which the surgery has impacted upon them in terms of financial, social, personal and physical costs and focuses on factors such as pain, disruption to their family, social and work lives and financial burden. The investment intervention will be tailored to the recent experiences of the participants. To this end the questions and responses are framed in such a way as to emphasise investment in the process of bariatric surgery in order to optimise the outcomes of the procedure. They will also complete a questionnaire at baseline then 3, 6 and 12 months after surgery.

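### The mediation sentence sets no time order between mediator and weight change, and its covariate rule would usually omit surgery type, so overlap or confounding could be reported as mechanism

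*Protocol article*

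**What the plan says.** The mediation analysis is the last of three analyses in the Data analysis section. It is to assess the role of "changes in beliefs about food, behavioural intentions and behaviour in predicting weight loss by follow up using mediation analysis". No visits are named for the mediator change or for the weight loss. The section's only covariate rule is that variables found to differ at baseline are added where needed.

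Four other parts of the article bear on this:

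- **Visits.** The Design section schedules beliefs, diet and exercise, "intentions to change their behaviour and weight at baseline (2 weeks pre surgery) and at 3, 6 and 12 months follow up". Primary outcome measures adds one weight: "This will be collected preoperatively 2 weeks before surgery, immediately after surgery and postoperatively at 3, 6 and 12 months follow up". So after baseline the mediators are never scheduled at a visit without a weight, and their first follow-up is at 3 months.
- **Intervention.** Participants in the investment arm "complete the investment based intervention at baseline (2 weeks pre surgery) then 3 and 6 months post-operatively".
- **Surgery type.** The Randomisation section allocates by type of surgery, and Primary outcome measures records it at baseline. Background cites a review in which mean excess weight loss for the "Roux-en-Y gastric bypass was 67% and for the gastric band was 42% at one year".
- **Beliefs and weight.** Background links successful surgery to "a role for a reduction in hunger, a decrease in the preoccupation with food and sense of improved control". It also says that in the pilot "the investment intervention resulted in an immediate change in participants’ beliefs about food and their intentions to change their diet and exercise behaviour", with the weight difference reported at 3 months.

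**The concern.** A mediation claim needs two paths: arm to mediator, and mediator to weight. Randomisation supports the first. The second is an observational comparison within a trial, open to reverse causation and to common causes.

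Both are plausible here. After a large operation, a patient who has lost more weight may think differently about food because of that loss. Surgery type may shift both appetite-related beliefs and weight. If the mediator interval overlaps the weight-loss interval and surgery type is left out, the model cannot tell these accounts from the hypothesised one.

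What is at stake is the explanation of how the intervention works. The estimated effect of the intervention on weight comes from the ANCOVA and does not depend on this model.

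**Working it through.** The article gives no figure for the mediation analysis, so there is none to reproduce. The check has three parts.

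**1. What the wording fixes.** Elsewhere (Background, Power calculation) the article uses the same phrasing, weight or weight loss by a follow-up visit, for the status reached at that visit. On that usage the outcome runs from baseline. The earliest follow-up of the mediators is 3 months after surgery, so even a 3-month mediator set against total weight loss overlaps with weight already lost by then.

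**2. What overlap does when beliefs have no effect on weight.**

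Inputs from the Power calculation: 60 completers per arm at 12 months; d = 0.3 from the pilot. Assumed, not from the documents: arm effect also at 0.5 SD; correlation g of weight loss with belief change 0.3 or 0.5; correlation of 3-month with 12-month weight loss 0.7; arm effect d the same at both visits; within-arm SDs of 1.

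Model: belief change M = g·W + √(1 − g²)·error, where W is weight loss to the same visit. Beliefs never affect weight. The arm-to-mediator path is then a = g·d in every analysis, and the mediator-to-weight path b is:

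- Same interval (0–12 months for both): b = g. Share mediated = a·b/d = g², giving 0.09 and 0.25.
- 3-month mediator, weight loss to 12 months, unadjusted: b = 0.7g. Share = 0.7g², giving 0.063 and 0.175.
- The same, adjusted for 3-month weight loss: b = 0, share 0.

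The true share is zero throughout. Simulation (2,000 trials per row, both paths required to be significant at two-sided 5%) gave:

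| d | g | Same interval: share | Same interval: false mediation | 3-month mediator, unadjusted: share | 3-month mediator, unadjusted: false mediation | Adjusted for 3-month weight: false mediation |
|---|---|---|---|---|---|---|
| 0.3 | 0.3 | 0.097 | 8.1% | 0.066 | 5.25% | 0.5% |
| 0.3 | 0.5 | 0.24 | 12.85% | 0.17 | 12.15% | 1.0% |
| 0.5 | 0.3 | 0.092 | 13.35% | 0.064 | 9.15% | 0.75% |
| 0.5 | 0.5 | 0.25 | 28.7% | 0.178 | 27.55% | 1.5% |

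The simulated shares match the formulas. The last-row rate of 28.7% has a Monte Carlo standard error of √(0.287 × 0.713 / 2000) ≈ 0.010, and repeat runs reach 30%. At the article's own d = 0.3, the same-interval rate is about 8 to 13%. Moving the mediator to 3 months does little without adjustment for 3-month weight.

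**3. What that adjustment costs.** If genuine mediation acts entirely by 3 months, 3-month weight lies on the causal path and adjusting for it removes the effect. A simulation assumed 60 per arm, an arm effect on beliefs of 0.6 to 1.0 SD, belief-weight correlation of about 0.5 to 0.6, the same 0.7 correlation and 3,000 runs. The unadjusted 3-month mediator detected the mediation in 89 to 99% of trials; the adjusted model did so in 4 to 6%.

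**Surgery type.** No rate was calculated for this part, and it rests on reasoning. The gap cited in Background is 67 − 42 = 25 percentage points of excess weight loss. Allocation by surgery type should balance the arms on it, so a rule triggered by baseline differences between arms will usually not bring it in. Balance between arms does not remove its influence on the relation between mediator and weight within arms.

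**The case against.** The strongest objection is that the sentence names no visits. A reader might infer that the plan pairs both changes over the same interval from baseline. The article does not say so, and its schedule would allow a time-ordered analysis. It is a condensed account; mediator windows may stand in a fuller protocol or SAP that is not shown. This stands: same-interval pairing cannot be called a stated error, and the absence of visit names is not itself the point. What remains is what the text does fix: an outcome worded as cumulative, and a covariate rule that would usually pass over surgery type.

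A reader might also infer that the protocol itself says weight loss drives beliefs. It does not. Background reports reduced hunger and preoccupation as playing a part in successful weight loss, and the pilot's sequence of immediate belief change followed by a weight difference favours the hypothesised direction. Reverse causation is possible, but the article does not assert it.

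Thirdly, a reader might take adjustment for 3-month weight to be the correct primary mediation model. Part 3 of the working shows why not: it exchanges false positives for near-total loss of any early effect, which is the pattern the pilot suggests. A 3-month mediator change also cannot reflect the 6-month intervention session.

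Finally, the highest rates need an arm effect of 0.5 SD, which the article does not give. That is fair, and the range has to be read with its assumptions.

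**Conclusion.** The concern holds in limited form. The planned mediation analysis relates mediator change to accumulated weight loss without placing one before the other, and its covariate rule would normally leave out surgery type. A positive result could therefore reflect weight loss changing beliefs, or surgery type acting on both.

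The size is illustrative: about 5 to 30% false mediation where the truth is none, resting on the assumed correlations and arm effects and on complete absence of a belief-to-weight path. The surgery-type part is unquantified. The matter is worth correcting but is confined to the mechanistic conclusion.

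**What to change.** In Data analysis:

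1. State that the mediation models include surgery type, baseline weight and the baseline value of the mediator, whether or not the arms differ on them.
2. State that any model in which the mediator and weight-loss intervals overlap will be described as an association, not as evidence of mechanism.
3. Add a sensitivity analysis of mediator change from baseline to 3 months against 12-month weight, adjusted for 3-month weight as well as the covariates in item 1. Say with it that it cannot detect mediation acting entirely before 3 months, so a null result there does not refute the hypothesis.

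All the variables and visits are already planned, so no further data collection is needed. The cost is slightly more analysis and a weaker mechanistic conclusion.

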### Randomisation

Once a patient is consented the researcher will use the third party blinded randomization process provided by the clinical trial unit at the University of Surrey to allocate them to either the investment based intervention condition or the control group, using random number tables according to surgery type.

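### Covariates beyond the baseline value are to be added because the arms look different at baseline, which selects on chance imbalance and tends to leave out surgery type

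*Protocol article*

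**What the plan says.** The Data analysis section of the protocol article sets the primary analysis as an analysis of "patient’s weight and BMI controlling for baseline measures using ANCOVA". Secondary outcomes go to repeated measures ANOVA, and a mediation analysis follows. The section then closes with a sentence that is not tied to any one of these: "Any baseline differences will be included as covariates in the analysis where necessary". It does not say which variables are eligible, what counts as a difference, or how necessity is judged.

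Two other sections bear on this. Under Primary outcome measures, "baseline measures of age, sex, height, type of surgery, educational level, and ethnicity will also be taken". Under Randomisation, patients are allocated "using random number tables according to surgery type", which I read as stratification by surgery type. The Data analysis section does not name surgery type as a covariate.

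**The concern.** In a randomised comparison, a baseline difference between arms is by construction a chance event. A difference says nothing about whether the variable predicts weight. A rule keyed to differences can therefore add a variable that explains nothing and pass over one that explains a great deal but is balanced.

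Surgery type is the clear case. The Background cites a systematic review with one-year excess weight loss of 67% for gastric bypass and 42% for gastric band. Allocation by surgery type should keep this factor close to balanced, so a difference-based rule would seldom pick it up. The analysis would then ignore the factor used in the randomisation and give up the precision that it offers.

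The second issue is that the set of extra covariates is settled only after the data are seen, and the qualifier about necessity leaves room for judgement at that stage. This is a rule that the article states, not a detail that it leaves to a later plan. An analysis plan that followed the sentence would inherit the problem.

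**Working it through.** The plan gives no figure on this point to reproduce, so the check has three parts.

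**1. How often would the rule change the model?**

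Inputs: six baseline variables (age, sex, height, type of surgery, educational level, ethnicity) from Primary outcome measures. Assumed, because the article is silent: a difference means p < 0.05, and the variables are independent.

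Chance that at least one of k variables differs = 1 − 0.95^k.

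- k = 6: 1 − 0.735 = 0.265.
- k = 5, leaving out surgery type because allocation balances it: 1 − 0.774 = 0.226.

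So the extra-covariate set would change through chance alone in roughly a quarter of such trials. Sex and height are correlated, so the true figure is somewhat lower than under independence.

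**2. What does the rule do to the type I error?**

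Simulation under no treatment effect, with 60 per arm (the 12-month figure in the Power calculation section), baseline weight always in the model, a two-sided 5% test and 10,000 runs per setting. Assumed: baseline–outcome correlation 0.7; one or five independent candidate covariates; multiple correlation R of the candidates with what baseline weight leaves unexplained of 0.3, 0.5 or 0.7. The Monte Carlo standard error near 5% is √(0.05 × 0.95 / 10,000) = 0.22 percentage points.

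| R | Candidates | All candidates fixed in advance | Added only if baseline p < 0.05 | Smallest p over several models |
|---|---|---|---|---|
| 0.3 | 1 | 5.02% | 4.84% | 6.60% |
| 0.3 | 5 | 4.87% | 4.86% | 7.77% |
| 0.5 | 1 | 5.05% | 4.32% | 7.49% |
| 0.5 | 5 | 4.78% | 4.47% | 10.17% |
| 0.7 | 1 | 5.11% | 3.84% | 8.68% |
| 0.7 | 5 | 4.93% | 3.59% | 12.71% |

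The fixed model is nominal. The mechanical rule is conservative, and more so as the candidates become more prognostic; at R = 0.3 the departure is within simulation error. The reason is that covariates enter only when they are imbalanced. In the other trials their variance stays in the residual, so the interval is wider than it need be.

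The last column takes the smallest p-value among the model without extra covariates, each one-covariate model and the full model, whether or not an imbalance is present. That is more freedom than the sentence gives. A second simulation came closer to its wording: 120 patients, baseline correlation 0.6, eight covariates each explaining 2% to 4% of variance, 20,000 runs. Mechanical selection gave 3.9% to 4.4%. Keeping the lower p-value of the models without extra covariates and with covariates picked for imbalance (at p < 0.05 or p < 0.2) gave 6.3%.

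**3. Is surgery type likely to be missed?**

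The Background figures differ by 67 − 42 = 25 percentage points of excess weight loss between the two operations. Randomisation uses surgery type; the Data analysis section does not. The only route for surgery type into the model is a baseline difference, which the allocation method is meant to prevent.

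**The case against.** Several points on the other side are sound.

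- **The primary model is not open.** Adjustment for the baseline value of weight and BMI is fixed, and that is probably the strongest predictor. A reader might infer that the whole adjusted model is left until after the data are seen. The text does not support that: only the additional covariates are open.
- **The plan does not build in inflation.** A reader might infer an excess of false positives. Followed mechanically, the rule gives the opposite. Inflation needs an analyst who compares results and keeps the better one, which the article does not plan. It only fails to rule it out.
- **Adjusting for a real imbalance is right.** In the simulation with one candidate and R = 0.5, among trials where that covariate differed at p < 0.05, the error rate was 19.4% without it and 3.4% with it. This supports adjustment for prognostic variables. It does not support waiting for a difference, since a covariate fixed in advance is in the model in those trials too.
- **Attrition.** The Power calculation section plans for 120 of 200 patients at 12 months, "assuming an attrition rate of 40% by 12 months". Among completers, differences can arise from unequal dropout as well as chance. That is fair, and the simulation does not model it, but the article does not give it as the purpose of the sentence.
- **Baseline measures may mean more than baseline weight.** The same words introduce the list of age, sex, surgery type and so on, so the ANCOVA might already include them. The Power calculation section, however, speaks only of controlling for baseline weight, and the closing sentence would have little to add on the wider reading.
- **Mediation.** Covariates are legitimate there, because the mediators are not randomised. This stands and limits the fix.

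**Conclusion.** The concern holds for the additional covariates. The rule selects on chance imbalance, not on prognostic value, and it tends to omit the factor used in the randomisation. This is a worthwhile wording correction, not a threat to the validity of the primary analysis.

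On size: about 26% for at least one difference among the six listed variables; a type I error of about 3.6% to 4.9% with some loss of precision if the rule is applied mechanically; about 6% or more only if models are chosen by result. The p < 0.05 trigger, the independence, the number of candidates and all correlations are assumptions, so these figures show direction and rough scale only. With a strict trigger and only two models to choose from, the inflation would lie closer to 5%. A higher chance of imbalance can be had by counting more variables (1 − 0.95^8 = 33.7% for eight), but the article's list has six.

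That surgery type is prognostic rests on the review figures in the Background. How much precision it would bring depends on the mix of operations in the trial, which the article does not give.

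**What to change.** For the between-arm comparisons, replace the closing sentence of the Data analysis section with a fixed covariate set: the baseline value of the outcome and surgery type, used whatever the observed balance. If age, sex or another variable is thought to predict outcome, name it now on those grounds. State that covariates will not be selected by baseline differences, and that any adjustment prompted by an observed imbalance is a labelled sensitivity analysis. Covariates for the mediation analysis can be specified separately.

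The cost is one sentence. Every variable named here is already collected, and neither the sample size nor the conduct of the trial changes.
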